This *Bridges-Round 2* (*hereafter Bridges-R2*) study proposes to examine the longitudinal impacts of the *Bridges* intervention on HIV risk prevention and care continuum outcomes among orphaned youth transitioning to young adulthood, a period characterized by unique vulnerabilities including increased experimentation, lower social control, and treatment non-adherence for those living with HIV [13,14]. Guided by the life course perspective [15], *Bridges-R2* will build on the *Original Bridges to the Future* study, to examine the longitudinal developmental and health outcomes [e.g., sexual risk-taking behaviors, HIV antiretroviral therapy adherence, pre-exposure prophylaxis (PrEP) use (for those who are HIV negative), optimizing health outcomes along the HIV care continuum, and potential mechanisms of effect of protective health behaviors] of the *Bridges* cohort. The study is guided by the following specific aims:

**Aim 1.** To examine the long-term impact of *Bridges* on: a) HIV prevalence (measured via participant’s HIV status) (primary outcome); and b) Explore in secondary analyses the long-term impact of *Bridges* on key developmental and behavioral outcomes (e.g., mental health, alcohol and drug misuse).

**Aim 2**. To elucidate the long-term effects of *Bridges* on potential mechanisms of change, including: a) economic stability, viral suppression (for adolescents living with HIV); PrEP use (for HIV negative adolescents), medical male circumcision (for boys); and b) young adult transitions.

**Aim 3:** To qualitatively investigate participants’ experiences with *Bridges* that may have influenced engagement with the program, sexual risk-taking decisions, financial behaviors; experiences with developmental transitions; and perceptions on program sustainability.

**Aim 4:** To assess the long-term costs and benefits of *Bridges* using formal economic evaluation.

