**Secondary Outcomes**		
Sexual risks	Timeline Follow Back (TFLB) [94,95], Adapted Youth Aids Prevention Project (used in Suubi & CHAMP) [96]	**T1-RC, 12, 24
Mental Health Functioning	Center for Epidemiological Studies-Depression Scale (CES- D) [97], PTSD Checklist [98], Brief symptom inventory [99]	**T1-RC, 12, 24
Financial/economic stability (Savings and asset)	Verifiable Bank statements, MIS IDA [100,101]; Self-Reports	**T1-RC, 12, 24
Adherence (for YLHIV)	Wilson self-report Questionnaire [102], viral load	**T1-RC, 12, 24
HIV testing	Self-report, verified by clinic records	**T1-RC, 12, 24
PrEP use (for HIV negative participants)	Self-report, verified by clinic records	**T1-RC, 12, 24
Medical Male Circumcision (for boys)	Self-report, verified by clinic records	**T1-RC, 12, 24

** T1-RC–Time 1 immediately following re-consenting.

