#### Biological assay

Mildmay, with internationally accredited laboratories by SANAS (https://www.sanas.co.za) will be responsible for collection of all biomarkers, participants’ counseling, notification, referral for treatment, follow-up and monitoring procedures for biological testing for HIV and viral load. Biological assay will be collected at T1 following reconsenting (T1-RC), and at 12 and 24-month post-reconsenting by Mildmay Medical Staff. HIV test results will be communicated to the participants by Mildmay.

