Exploratory analyses will explore for all participants the superiority of a) *Bridges* to control, b) *Bridges PLUS* to control, and c) *Bridges PLUS* to *Bridges* in lowering the odds of engaging in sexual risk taking, the odds of problem alcohol and substance use behaviors, and increasing mean levels of mental health functioning among study participants. Subgroup analyses will perform the same comparisons for HIV testing and PrEP use for the subset of participants not living with HIV; a parallel set of analyses will perform the same comparisons for ART adherence and HIV care engagement for youth living with HIV. The same GLMM approach described above will be extended to three levels to model the odds of binary outcomes across time using the same fixed effects (study arm, time, and study arm-by-time), a random effect for the school level (random intercepts), and adding random effects for the person level (random intercepts, random slopes, and their covariance). For the continuous mental health exploratory outcomes, we will fit linear mixed models (LMMs).

To maximize rigor, the assumptions of normality and constant variance of residuals in LMMs will be evaluated by examining histograms of the residuals and scatter plots of predicted values-by-Cholesky-scaled residuals, respectively. Transformations of outcomes will be utilized as needed to improve data conformance with model assumptions. Inferences for models whose residual statistics still do not fully meet assumptions following transformations will be generated via robust heteroskedastic-consistent estimators [116]. Group comparisons will be performed via three pairwise time-averaged comparisons across repeated measurements. Alpha (α) will be set at .05/3 = .017 to maintain a nominal α = .05 per outcome. Any additional post-hoc comparisons (e.g., paired comparisons of groups at each time point) will maintain nominal α = .05 through the use of simulation-based stepdown multiple comparison methods [117]. All analyses will include outlier and influential case screening via computation of Cook’s D, DFBetas, and likelihood displacement statistics. If outliers are found, results will be reported with and without outliers included [118,119].

#### Primary analyses for Aim 2

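### HIV testing, PrEP use, adherence and care engagement are compared by arm within subsets defined by the primary outcome, so these exploratory contrasts are not randomised comparisons if the arms differ in HIV

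*Protocol article*

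**What the plan says.** All references are to the protocol article.

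- **Secondary exploratory analyses for Aim 1.** The section opens "Exploratory analyses will explore for all participants the superiority of" each arm pair. It then narrows: "Subgroup analyses will perform the same comparisons for HIV testing and PrEP use for the subset of participants not living with HIV", and "a parallel set of analyses will perform the same comparisons for ART adherence and HIV care engagement for youth living with HIV". On the contrast it says: "Group comparisons will be performed via three pairwise time-averaged comparisons across repeated measurements". Alpha is .017 per comparison, as for the primary outcome.
- **Aim 1 and Table 2.** HIV status, by biological assay, is the primary outcome. H1a to H1c (Primary analyses for Aim 1) state that it will differ between arms.
- **Time points used in proposed inferential analyses.** Biomarkers exist only in Bridges-R2, so no assay at randomisation can define the subsets instead.
- **Biological assay.** HIV is assayed at T1-RC, 12 and 24 months, and "HIV test results will be communicated to the participants by Mildmay".
- **Table 2.** HIV testing is also an outcome at those three waves, measured as "Self-report, verified by clinic records".
- **Aims and Cost-Benefit Analysis for Aim 4.** Viral suppression and PrEP use are named under Aim 2, and their differences are given a monetary value in Aim 4.

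**The concern.** Randomisation makes the arms comparable as wholes. It does not make the HIV-negative members of one arm comparable with those of another once the arm may have changed who is HIV-negative. If the intervention prevents infections, its HIV-negative subset includes people who would have been infected under control, and its HIV-positive subset lacks their counterparts. Eligibility for the Original Bridges study did not exclude children already living with HIV, so the positives can mix early and later infections in proportions that differ by arm. An arm difference in PrEP use or adherence could then reflect composition alone.

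The contrasts therefore lose the protection of randomisation exactly when the main hypothesis is true. At stake are results on prevention and engagement in care, which the abstract names as open questions, and possibly the Aim 4 valuation.

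For HIV testing there is a separate risk. The study itself tests every participant at each wave at which the outcome is recorded, and the contrast averages over those waves.

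**Working it through.** **1. The plan's own figure.** Inputs from Statistical power analysis: N = 799, control prevalence 19.7%, ICC .12, alpha .017, power .80. The 48 schools come from the overview of the Original Bridges study.

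- Design effect: 1 + (799/48 − 1) × .12 = 2.877.
- Effective n per arm: (799/3)/2.877 = 92.6.
- A two-sided pooled two-proportion calculation gives 80% power at a difference of .153. The stated 15.3 points reproduces, and implies 19.7% vs 4.4%.

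No stated number is disputed. The figure only sizes the subsets. It is a minimum detectable difference, not a forecast, so 15% and 10% intervention prevalence are shown as well; both are assumptions.

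**2. Subset sizes and composition at the final wave**, with 799/3 ≈ 266 per arm and an intervention that only prevents infections. With intervention prevalence p:

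- prevented share of the intervention HIV-negative subset = (.197 − p)/(1 − p);
- share of control positives with no intervention counterpart = (.197 − p)/.197.

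| p | HIV-positive, control vs intervention | Prevented share of negatives | Control positives without counterpart |
|---|---|---|---|
| 15% | 52 vs 40 | 5.5% | 24% |
| 10% | 52 vs 27 | 10.8% | 49% |
| 4.4% | 52 vs 12 | 16.0% | 78% |

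**3. Adherence with no true effect.** Assume 3% of each arm was infected before randomisation, with adherence 60% in those and 80% in later infections. Observed adherence = .80 − .20 × (.03/prevalence).

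- Control: .80 − .20 × .152 = 77.0%.
- p = 15%: .80 − .20 × .200 = 76.0%, gap about 1 point.
- p = 10%: .80 − .20 × .300 = 74.0%, gap about 3 points.
- p = 4.4%: .80 − .20 × .682 = 66.4%, gap about 11 points.

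Reverse the assumption (80% early, 60% later) and let 25% to 50% of control cases be early. The intervention arm now looks better: odds ratio 1.07 to 1.17 at p = 15%, and 1.25 to 1.68 at p = 10%. The sign is not known in advance.

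**4. PrEP use with no true effect.** Assume 10% use among those negative under either arm and 0% to 30% among those whose infection was prevented. The spurious odds ratio is 0.94 to 1.12 at p = 15%, 0.88 to 1.25 at p = 10%, and 0.83 to 1.37 at p = 4.4%.

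**5. If the arms do not differ in HIV**, p = 19.7%, every prevented share is zero and the bias vanishes.

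**6. HIV testing.** Let outside testing be a and b in the two arms, and let a counted study test reach a share c of participants. The observed difference is (b − a)(1 − c). With a = 50% and b = 60% (assumed), 10 points become 1.0, 0.5 or 0 at c = 90%, 95% or 100%. In simple averaging, a 15-point gap at T1-RC followed by none at 12 and 24 months gives (15 + 0 + 0)/3 = 5 points. The planned contrast is on the logit scale, so this is only a guide. If study tests do not count, c = 0 and this dilution does not arise.

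**The case against.** A reader might infer that these contrasts are biased or empty outright, and that recorded HIV testing will be close to universal in every arm. The documents do not support either reading.

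- The bias needs an arm effect on HIV. The 11-point example uses the minimum detectable difference, a 78% relative reduction; more modest effects give 1 to 3 points. Even 77% vs 66% with 52 vs 12 youth is about 0.7 standard errors (.106/.149) before clustering. Nothing in the article supports the 3%, 60% or 80%.
- Emptiness is not shown for PrEP use, adherence or care engagement. The last two would be imprecise, which is different.
- Near-universal testing would require that study tests count and fall within the recall period. Table 2 lists HIV testing separately from the assay. The item wording and look-back belong to a questionnaire or full protocol not shown, so their absence is no fault.
- The model has an arm-by-time term, and comparisons at single waves are foreseen, though only post hoc.
- The analyses are labelled exploratory, and PrEP use and adherence have meaning only within these subsets.
- All-participant composites partly re-measure HIV. With identical 70% suppression, positive and unsuppressed is 5.9% vs 1.3% at 19.7% vs 4.4%; with identical 10% PrEP uptake, negative and on PrEP is 8.0% vs 9.6%.

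All of this stands as a limit on size and certainty. It does not remove the structural point: superiority comparisons at alpha .017 are planned inside subsets formed by the outcome, with no caveat, and the exploratory label does not tell a reader that randomisation no longer protects them.

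**Conclusion.** The concern holds in a conditional form. All four outcomes are compared within subsets set by the post-randomisation primary outcome, so the comparisons are not randomised ones if H1a to H1c are right. The bias is nil without an arm effect on HIV, probably small in the HIV-negative subset, and potentially larger among youth living with HIV; its direction cannot be known from the documents. All adherence, PrEP and outside-testing values, and the 15% and 10% prevalences, are illustrative. Only 19.7% and the 15.3-point difference come from the article.

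The testing point is a risk that depends on whether study tests count. Even if they do not, being tested by the study may reduce the reason to test elsewhere at 12 and 24 months, so T1-RC is the cleanest wave. The matter is moderate and does not touch the primary analysis.

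**What to change.** - Add two outcomes analysed in all participants with the same arm contrasts: HIV-positive and not virally suppressed (yes/no), and HIV-negative and on PrEP (yes/no). State that each combines the effect on HIV with the effect on care or PrEP, and read them beside the subset results.
- Keep the subset contrasts, but report them as descriptive and conditional on HIV status measured after randomisation. Say the same wherever they feed the Aim 4 valuation. The article does not say whether Aim 4 uses whole-arm or subset differences, so state which.
- Define the testing outcome as HIV tests outside the study. Ask the T1-RC item before the study test and make that wave the main testing contrast, with later waves as support. Within the HIV-negative subset it remains a conditional comparison.

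The cost is plan wording, one clarifying questionnaire item and slightly more analysis, using assays and viral loads already planned. The downside is that composites are harder to interpret than adherence or PrEP use alone.

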#### Exploring mediation and moderation

Exploratory analyses will explore whether the potential mechanisms of change included in Table 2 mediate the relationships between intervention group assignment and CR-HIV, economic stability, positive youth transitions and social support, and whether geographic location, exposure to other HIV/STI prevention programs, household income and asset accumulation moderate those associations. Analyses will be conducted using principles of structural equation modelling (SEM) and causal inference [120]. M*plus* will be used to fit mediation and moderation models because it can adjust standard errors for clustering of participants within schools and because it unites causal inference and SEM-based analyses in the same software platform [121].

#### Exploring trajectories of change over the full developmental period captured by the *Bridges* project

Moderator, mediator, and sexual behavior and mental health outcome data will be available at 8 time points from the start of *Original Bridges* through the end of *Bridges-R2*. We will initially explore trajectories of these variables by generating spaghetti plots of participants’ individual trajectories with intervention group averages overlaid to visualize group average (i.e., mean) levels of change and inter-participant variability. Next, we will fit mixed effects growth models to investigate whether change over time can be quantified using low-dimensional parametric functions (e.g., linear, quadratic) of explanatory variables. Finally, we will employ the highly flexible time-varying effect modeling (TVEM) to go beyond simple parametric functions to describe the form of changes in variables over time. TVEM allows the effects of covariates on outcome trends to vary over time non-parametrically [122,123]. TVEMs will be fitted using the % weighted TVEM SAS macro produced by the Penn State Methodology Center, a leader in developing longitudinal analysis methods and software.

#### Sex as a biological variable

All previously described analyses will be repeated with models extended to include sex assigned at birth as a moderator to examine whether effects vary by participant sex. For male participants, we will perform additional exploratory analyses at each time point using a three-level GLMM to explore whether medical male circumcision differs by intervention group.

#### Qualitative data analysis for Aim 3

All interviews will be transcribed and translated from Luganda into English. Transcripts will be compared with digital records to ensure transcription accuracy. All transcripts will be uploaded to QSR NVivo12 analytic software for data analysis. Interview transcripts will be reviewed by the research team to develop a broad understanding of content as it relates to the project’s specific aim and to identify topics of discussion and observation. During this step, as well as during subsequent steps, analytic memos will be written to further develop categories, themes, and subthemes, and to integrate the ideas that emerge from the data [124]. Using analytic induction techniques [125], transcripts will be read multiple times for initial coding by the research team. For initial coding, randomly selected 10 interview transcripts will be read multiple times and independently coded by the project investigators using a priori (i.e., from the interview guide) or emergent themes (also known as open coding) [124]. Broader themes/ categories will be broken down into smaller, more specific units until no further subcategory is necessary. Qualitative findings will also shed light into potential mediators and moderators for sexual risk-taking and mental health.

The codes and definition boundaries of specific codes (inclusion and exclusion criteria for assigning a specific code) [125] will be discussed during research team meetings to create the final codebook. Each text will be independently coded by two investigators using the codebook. Inter-coder reliability will be established. A level of agreement from 66 to 97% depending on level of coding (general, intermediate, specific), indicates good reliability in qualitative research [126]. Disagreements will be resolved through discussion during team meetings. The secondary analysis will focus on comparing and contrasting themes and categories within and across groups to identify similarities and differences. To further ensure rigor, study results will be presented to study participants who participated in the interviews, enabling them to provide comments on results and suggest modifications or additional avenues of investigation when possible (member checking) [127]. An audit trail of data collected as well as memos and minutes of team meetings will be kept throughout the study [127].

#### Cost-Benefit Analysis (CBA) for Aim 4

The *Original Bridges* study used cost-effectiveness analysis (CEA) a tool for evaluating the costs of producing a given level of outcome [11]. CEA allows users to compare different approaches (*Bridges* or *Bridges PLUS*) for achieving these outcomes and to identify more efficient ones—those with a smaller Incremental Cost-Effectiveness Ratio (ICER), the $/outcome (in USD or local currency, UGX), relative to a status quo (“usual care”). CBA in this study builds upon the CEA by valuing (monetizing) all outcomes of *Bridges* in USD (and UGX), facilitating critical assessments and comparisons for sustainability and scalability. Building on the cost data in our previous CEAs, and continued evaluation in *Bridges-R2*, we will use CBA methods [128,129] to: 1) value gains observed since the start of *Bridges and Bridges PLUS* and 2) develop lifecycle economic models of projected future earnings, health trajectories, and social improvements. In Aim 1, the net change in HIV prevalence will be valued (prospectively) as the survival-adjusted lifecycle costs of HIV in DALYs from the GBD [130,131] converted to UGX & USD [132]. We will use a similar approach for the difference in mental health and substance misuse, secondary outcomes in Aim 1; that is, the change in rates will be measured in DALYs which are then monetized. If rates decrease, *costs avoided* are a benefit to *Bridges-R2*, and if rates increase, costs incurred reduce the net benefit. For Aim 2, the difference in viral suppression, PrEP use, and circumcision has both a cost (increased health care services) and a benefit (reduced risk of adverse health outcomes). The health benefits of viral suppression, PrEP use, and circumcision will be taken from the literature and valued in DALYs converted to UGX and USD as above. For economic stability, the present timing as YPoAIDS in *Bridges* transition into young adulthood is ideal: models will be based on actual earnings and assets. In pure economic value, we anticipate that the gains in earnings via improved human capital and financial behaviors will be the largest direct economic benefit. Following economic evaluation standards [133], we will report the CBA from 3 perspectives (participants, funders, and society), discount benefits and costs to their present value, and conduct sensitivity analyses around valuation parameters, modeling of future effects, and discounting.

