### Data collection

#### Quantitative assessments

Assessments will occur at baseline following reconsenting, 12, and 24-months and will take place at the ICHAD’s field offices in Masaka or satellite sites (including health clinics) for study collaborators: Mildmay or Reach the Youth (RTY) Uganda, with each lasting about 60–90 minutes. Interviews will be conducted by interviewers fluent in Luganda and English depending on participant’s English proficiency. A list of standardized instruments that will be included in the main statistical analyses are outlined in Table 2. All measures used have been pre-tested and made culturally appropriate to the Ugandan context in our ongoing Suubi+Adherence-R2 study [79]. Assessments capturing non-sensitive information, for example, sociodemographic information, mental health functioning, psychosocial well-being and social support are administered orally but recorded using Qualtrics–a computer assisted survey implementation program.

**Table 2 pone.0284572.t002:** *Bridges-R2* study measures.

Variable	Measurement	Timepoint

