#### Time points used in proposed inferential analyses

To maximize the rigor of the analyses; to assure alignment of biomarker data (only measured in the *Bridges-R2*) and our remaining outcomes; and to avoid reuse of *Original Bridges* study outcomes (already examined for shorter-term intervention efficacy) and biased examination of longer-term intervention efficacy, all proposed primary inferential analyses and most of the proposed secondary inferential analyses listed will use only *Bridges-R2* data. The exception is longitudinal developmental trajectory analyses proposed to explore associations between changes in time-varying covariates and mechanisms of change with outcomes measured across both studies.

#### Primary analyses for Aim 1

We hypothesize that: H1a. Relative to the control group, participants in the *Bridges* intervention group (1:1 savings incentive match rate) will have a lower odds of HIV infection at the final measurement point; H1b. Relative to the control group, participants in the *Bridges PLUS* intervention group (1:2 savings incentive match rate) will have a lower odds of HIV infection at the final measurement point; and H1c. Relative to the *Bridges* intervention group, participants in the *Bridges* PLUS intervention group will have a lower odds of HIV infection at the final measurement point. To test H1a-H1c, we will fit a two-level generalized linear mixed model (GLMM) with fixed effects for study arm, time, and their interaction. We will use random intercepts for school ID to account for clustering of persons within schools. Reflecting the binary HIV status outcome, a binomial distribution and logit link will be used. To test H1a-H1c we will perform three pairwise planned comparisons. Alpha (α) will be set at .05/3 = .017 for these three comparisons to maintain a nominal α = .05. We will adjust for orphanhood status, the only covariate where imbalance was detected in our *Original Bridges* data. It is important to note that previously, deaths have been very few; however, if numbers of deaths become non- trivial, we will extend our proposed GLMMs to jointly model survival and the odds of HIV infection simultaneously [115].

#### Secondary exploratory analyses for Aim 1

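### The three-level logistic model planned for male circumcision leaves the size of its arm odds ratio arbitrary or uninterpretable; a two-level model at each wave would not (minor)

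*Protocol article*

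**What the plan says.** The section on sex as a biological variable plans, for male participants, "additional exploratory analyses at each time point using a three-level GLMM to explore whether medical male circumcision differs by intervention group".

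What three levels means is fixed in the secondary exploratory analyses for Aim 1: "The same GLMM approach described above will be extended to three levels to model the odds of binary outcomes across time", with a school random intercept and "adding random effects for the person level (random intercepts, random slopes, and their covariance". The levels are therefore measurements within persons within schools.

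The primary analysis for Aim 1 contains a simpler form: "We will use random intercepts for school ID to account for clustering of persons within schools", and "a binomial distribution and logit link will be used". That is a two-level logistic model with no person level.

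Table 2 lists the outcome, "Medical Male Circumcision (for boys", among the secondary outcomes, by self-report verified against clinic records, at all three visits: "Assessments will occur at baseline following reconsenting, 12, and 24-months". The cost-benefit section for Aim 4 mentions it once more: "For Aim 2, the difference in viral suppression, PrEP use, and circumcision has both a cost".

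**The concern.** A person-level random effect needs more than one observation per person, and observations that vary within the person. The circumcision sentence can be read as a separate model at each wave, or as contrasts at each wave from one model over all waves. In the first case each man has a single value. In the second he has up to three values that can only move from no to yes, so most men have the same value throughout. The person variance is then either not estimable or very large.

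In a logistic mixed model the arm odds ratio is conditional on the person effect, and its size scales with that variance. What is at stake is whether the reported odds ratio and its interval have a usable size.

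**Working it through.** **Plan's own figure.** None is given for circumcision. The only power figure is for HIV prevalence, and it reproduces. There are 799/3 = 266.3 participants per arm, or 16.65 per school. The design effect is 1 + (16.65 - 1) x 0.12 = 2.88. Power for 19.7% versus 4.4% at two-sided alpha .017 is then 0.798 (stated .80), and h = 0.497 (stated .499). It is unaffected by this point.

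**Assumptions not in the document.** The number of men, circumcision rates and arm effects are not stated, so the values below are illustrative. That circumcision does not reverse is taken as plain fact. The fits use random intercepts only; the planned random slopes would weaken identification further.

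**1. One wave, no school effect.** Assume 39/130 (30%) versus 57/130 (44%). For any person SD s, the marginal probability is p = the average of expit(a + s·b) over a standard normal b. For every s some value of a gives exactly the observed p, so the maximum log-likelihood is always

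39 ln(0.300) + 91 ln(0.700) + 57 ln(0.438) + 73 ln(0.562) = -168.53.

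The conditional log odds ratio grows roughly as ln(1.82) x sqrt(1 + s²/2.9).

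| Person SD | Max log-likelihood | Arm OR (exact fit) | Arm OR (approximation) |
|---|---|---|---|
| 0 | -168.53 | 1.82 | 1.82 |
| 1 | -168.53 | 2.05 | 2.0 |
| 2 | -168.53 | 2.65 | 2.5 |
| 4 | -168.53 | 5.04 | 4.6 |

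**2. One wave, school random intercept included.** One simulated data set: 400 men (about half of 799) in 48 schools, 45% of controls circumcised at T1-RC, 7% new per interval, Bridges PLUS log odds ratio 0.5, school SD 0.5. At the final wave, across person SD 0 to 8, -2LL changes by 0.02 (542.87 to 542.89). The odds ratio for Bridges PLUS versus control runs from 1.77 to 18.2, and z stays at 2.01.

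**3. Three waves jointly, same data set.** Final-wave proportions were 0.492 (control) and 0.625 (Bridges PLUS), a crude odds ratio of (0.625/0.375)/(0.492/0.508) = 1.72. The person SD was held at each value in turn, with fine-grid integration. The right-hand columns repeat the exercise with 2% random misreporting.

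| Person SD | -2LL, no reversals | Final-wave OR | z | -2LL, 2% misreported | Final-wave OR | z |
|---|---|---|---|---|---|---|
| 0 | 1577.9 | 2.04 | 1.90 | 1587.5 | 2.07 | 2.02 |
| 2 | 1066.3 | 3.22 | 1.92 | 1127.4 | 3.25 | 2.06 |
| 4 | 886.5 | 6.17 | 1.92 | 980.9 | 6.13 | 2.07 |
| 8 | 793.4 | 23.2 | 1.92 | 923.5 | 21.7 | 2.09 |
| 16 | 754.1 | 347 | 1.94 | 923.1 | 264 | 2.09 |
| 32 | 739.9 | 90,000 | 1.95 | 953.0 | 34,900 | 2.09 |

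Without reversals the fit keeps improving, with no optimum up to SD 32. With misreporting there is an optimum, at an SD of about 8 to 16, where the odds ratio is about 22 to 264.

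**4. What stays stable.** In a second simulated three-wave data set (133 men per arm, assumed 40% versus 55% at T1-RC, 5% new per interval), the odds ratio rose from 1.9 to above 300,000 between SD 0 and 32. The model-implied final-wave proportions stayed at 0.47-0.49 versus 0.63-0.65, a difference of 15 to 17 points.

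**5. Person level removed.** On the final wave of the first data set, the two-level model gives one identified answer: OR 1.77, SE of the log odds ratio 0.285, z 2.01, school SD 0.35.

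**The case against.** **The sentence may mean contrasts from the longitudinal model.** This is probably the more natural reading, since the Aim 1 exploratory section describes post hoc group comparisons by time point in similar terms. It removes the single-wave problem but meets the one in step 3.

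**The odds ratio need not be arbitrary.** Status is self-reported and checked against clinic records, so a few recorded reversals are plausible and would give the likelihood an optimum. This stands. The odds ratio is then identified, but at 22 to 264 for a difference of some 13 points (0.492 versus 0.625) it is not interpretable. It would be too strong to say that software settings alone determine the estimate in every case.

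**The test is sound.** Direction and z hardly move, and software that sets the person variance to zero returns the valid two-level result. This stands and limits the severity.

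**The cost-benefit analysis.** A reader might infer that a distorted odds ratio passes into Aim 4. The document does not support that. The cost-benefit section speaks of a difference in circumcision, does not say which estimate it takes, and nowhere uses an odds ratio. The model-implied difference in proportions is stable, so no harm to Aim 4 is shown.

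**It is exploratory.** Correct: circumcision is not in H2a to H2c and has no bearing on the primary HIV analysis.

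**Conclusion.** The specification is wrong as written under both readings. At a single wave the person variance is not identified and the likelihood is flat. Over three waves it is driven towards infinity or, with slight misreporting, to a very large value. The size of the odds ratio and its confidence interval are therefore arbitrary or uninterpretable; the z statistic, the direction and the model-implied proportions are nearly unaffected.

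The flat or ever-improving likelihood follows from the data structure and does not depend on the assumed rates. The particular odds ratios do depend on them, and the three-wave tables rest on one simulated data set per scenario. Severity is minor.

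**What to change.** Replace the three-level model in the sentence on circumcision with the two-level logistic model of the Aim 1 primary analysis, restricted to male participants and fitted separately at each wave: school random intercept, study arm and orphanhood status, and no person-level random effects. Report the arm difference in proportions alongside the odds ratio; that difference is also the quantity suited to the cost-benefit section.

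The cost is one sentence and a simpler model, with one small downside. A per-wave model drops men missing at that wave, and the plan allows a fall from 999 to 799 participants. A recorded circumcision can be carried forward, since the status is known once positive, or the multiple imputation already planned for incomplete data can be used. If statuses are carried forward, men still uncircumcised when last seen should be imputed, because filling in only the known positives would overstate the proportion circumcised.
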